## Methods/Design

After the positive vote of the ethics committee of the Faculty of Medicine, Ruprecht-Karls University of Heidelberg, Germany, enrollment of the study subjects has been started in June 2007 in this randomized controlled double blind single center clinical trial as a pilot study on the safety and tolerance of preoperative melatonin application in patients undergoing major liver resection. Patients are considered for recruitment to the study according to inclusion and exclusion criteria (Table 1). The duration of the trial for each subject is expected to be 9 days, i.e. 1 day before operation (day -1), the day of operation (day 0) and the first 7 days following the operative procedure (postoperative days 1–7). Considering a recruitment rate up to 5 cases per month, the overall duration of the trial is expected to last approximately 8–10 months. A drop-out rate of 10% (due to non-compliance, intolerance, premature discontinuation, lost to follow-up, etc) will increase the total duration of trial to about 12 months. The actual overall duration of recruitment may vary due to the availability and consent rate of patients undergoing major liver resection.

**Table 1 T1:** Criteria of inclusion and exclusion of patients.

**Inclusion criteria**	**Exclusion criteria**
patients meeting all of the following criteria are considered for inclusion in the study:	patients with any of the following will not be included in the trial:
- scheduled for elective major partial liver resection of ≥3 liver segments for liver neoplasms	- patients <18 and >90 years
- written informed consent	- patients <50 and >120 kg
- adequate contraception is required for women with childbearing potential	- patients with severe, organ-specific disorders (e.g., liver or renal failure, acute pancreatitis)
	- patients undergoing emergency procedures
	- patients with expected intubation problems
	- pregnancy and/or lactation
	- history of hypersensitivity to the investigational product or to any drug with similar chemical structure or to any compound present in the pharmaceutical form of the investigational product
	- simultaneous participation in another clinical trial
	- mental condition rendering the subject incapable of understanding the nature, scope, and consequences of the trial
	No subject will be enrolled in this study more than once.

Before operation demographic data, medical history, physical examination, diagnosis, therapy, as well as comorbidities and concomitant medications are documented on day -1. Furthermore, routine laboratory measurements and substrate monitoring are carried out and documented (Table 2). On the day of surgery and following intubation for general anaesthesia, 500 ml milk containing test (melatonin; Helsinn Chemicals, Biasca, Switzerland) or placebo product (microcrystalline cellulose) (50 mg/kg BW) is administered via a standard gastric tube placed right after intubation of the patient. Clinical laboratory values (including chemistry, hematology, liver laboratory tests, and cytokines) and the substrates are measured on the day of operation and daily throughout the entire postoperative study period of 6 days. Clinical outcome parameters include infectious (pneumonia, wound infection, peritonitis, urinary tract infection, sepsis) as well as non-infectious (bilioma, bile fistula, pleural effusion, bleeding, circulatory insufficiency, renal insufficiency, wound dehiscence, intestinal obstruction/ileus, pulmonary embolism) complications. Sepsis is defined as the presence of at least 2 out of the following 4 criteria: (1) temperature >38°C or <36°C, (2) tachycardia >90/min, (3) respiratory insufficiency (1 out of 3 criteria: respiratory rate >20/min, hyperventilation with PaCO2 <32 mmHg or PaO2 <70 mmHg (spontaneous breathing) or PaO2/FiO2 <175 mmHg (mechanical ventilation), and (4) leukocytosis >12/nl or leukopenia <4/nl. Renal failure is defined according to RIFLE-criteria [31]. The schedule for all study related activities and data collection is listed in Table 2.

**Table 2 T2:** Flow chart, PORTAL study

**Phase**	Pre-OP day^1^	OP day^1^	Post-OP day 1–7^1^
**Study-day**	-1	0	1–7
Medical history	X		
Physical examination	X		
Inclusion/exclusion criteria	X		
Karnowsky index	X		
Patient information	X		
Patient informed consent	X		
Concomitant medication	X		X
Documentation of surgery (OPS code)		X	

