## Background

Surgical injury triggers a proinflammatory cascade of hormonal, immunologic, and cellular responses collectively known as acute phase response to minimize damage and to hasten healing and recovery as John Hunter once described it as "both the disposition and the means of cure [1]." However, the consequences of this sophisticated sequence of events are not always advantageous for the surgical patient due to the varying magnitude of the response and the severity of the injury. Tissue ischemia and the subsequent reperfusion, particularly in visceral organs, as well as loss of intra- and extravascular volume due to hemorrhage, burn injury or extracorporeal circulation can result in oxidative stress, in both surgical and distant sites, microvascular leakage, platelet aggregation, leukocyte-endothelium adhesion, and depression of humoral and cell-mediated immunity that subsequently lead to proinflammatory changes [2]. Systemic endotoxinemia is accentuated due to the leakage of aerobic and anaerobic microflora from the gastrointestinal tract through microvascular damage resulting from ischemia/reperfusion injury, altered immunity secondary to the inflammatory cascade, visceral ischemia and necrosis, hemorrhage and hypotension [3]. Under these circumstances the occurrence of transient endotoxinemia and formation of free radicals is almost certain with both infectious and non-infectious postoperative complications as possible consequences. Surgical infections, identified as a major limiting factor to the postoperative clinical recovery, do occur in spite of preventive treatment with antibiotics immediately before or during surgical treatment and represent a major challenge especially when more complex and high-risk operations are performed in more debilitated patients, and in the face of increasing antibiotic resistance.

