### Objectives and endpoints

The primary aim of this pilot study is to evaluate safety and tolerance of preoperative application of melatonin in patients undergoing operative procedures for partial liver resection. In addition, clinical parameters reflecting pathophysiological functions of the liver will be determined.

Data on clinical outcome (infectious and non-infectious complications) are collected as secondary endpoints to allow a power calculation for a randomized clinical trial aiming at clinical efficacy (Table 2).

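### Sepsis is counted as an infectious complication but defined by inflammatory signs alone, so patients without infection can be scored as septic

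*Protocol article*

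**What the plan says.** Methods/Design of the protocol article divides the clinical outcomes into infectious and non-infectious complications and puts sepsis in the first group: "Clinical outcome parameters include infectious (pneumonia, wound infection, peritonitis, urinary tract infection, sepsis".

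The definition follows in full: "Sepsis is defined as the presence of at least 2 out of the following 4 criteria". The four are:
- "1) temperature >38°C or <36°C, (2) tachycardia >90/min";
- "respiratory insufficiency (1 out of 3 criteria: respiratory rate >20/min", with blood-gas alternatives;
- "leukocytosis >12/nl or leukopenia <4/nl".

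No infection, suspected or proven, is part of the rule, and no other section adds one. Table 2 has sepsis recorded over postoperative days 1 to 7. Table 1 restricts the trial to elective resections of three or more liver segments.

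Objectives and endpoints says that the complication data "are collected as secondary endpoints to allow a power calculation" for a later efficacy trial. The Abstract says the same.

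**The concern.** All four criteria are signs of systemic inflammation. The Background opens its argument with this response: "Surgical injury triggers a proinflammatory cascade of hormonal, immunologic, and cellular responses". Every patient has a major resection, and sepsis is scored in the week after it, when such a response is to be expected. As written, a patient with a pulse of 92/min and leukocytes of 12.5/nl on day 1 has an infectious complication, whatever the cause.

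Two things are at stake.

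1. **The planning rate.** The complication rates are meant to size the next trial. If uninfected patients enter the sepsis count, its rate is too high and any true effect on sepsis is diluted.
2. **The meaning of a difference.** The Trial rationale proposes that melatonin damps the inflammatory response to surgical injury. A drug that lowers temperature, pulse or leukocyte count would reduce sepsis as defined without preventing an infection.

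**Working it through.** **Text check.** The outcome list keeps infectious and non-infectious events apart. The sepsis rule uses only signs that do not tell the two apart. Because the rule is written out with numerical cut-offs, the missing infection criterion is a feature of the stated definition and not a detail lost when the protocol was condensed.

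**No figure to reproduce.** The article gives 40 patients but no event rate, effect size, alpha or power. All rates below are assumptions; the calculations show direction and possible size only.

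**1. Dilution.** Let *p* be the true sepsis rate and *s* the share of non-septic patients who meet two signs at some time in the seven days. Assume that every truly septic patient meets the rule and that *s* is equal in both arms. Then

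measured rate = *p* + (1 − *p*)*s*.

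With *p* = 0.10 vs 0.05 (true risk ratio 0.50):

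| *s* | Control | Melatonin | Measured risk ratio |
|---|---|---|---|
| 0.30 | 0.10 + 0.90 × 0.30 = 37% | 0.05 + 0.95 × 0.30 = 33.5% | 0.91 |
| 0.60 | 0.10 + 0.90 × 0.60 = 64% | 0.05 + 0.95 × 0.60 = 62% | 0.97 |
| 0.90 | 0.10 + 0.90 × 0.90 = 91% | 0.05 + 0.95 × 0.90 = 90.5% | 0.99 |

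**2. Effect on the next trial's size.** Two proportions, 80% power, two-sided 5%, pooled formula, where p̄ is the mean of the two rates:

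n per arm = [1.960√(2p̄(1 − p̄)) + 0.842√(p₁(1 − p₁) + p₂(1 − p₂))]² / (p₁ − p₂)².

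- Halving the inflated 64%, to 32%: (1.385 + 0.563)² / 0.1024 = 37.06, so 38 per arm.
- Halving the true 10%, to 5%: (0.730 + 0.312)² / 0.0025 = 434.4, so 435 per arm.
- Power of 38 per arm for 10% vs 5%: (0.05√38 − 0.730) / 0.371 = −1.14, which is about 13%.

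**3. Second set of assumptions.** With true infection at 15% vs 7.5%, the same formula gives 278 per arm. If 20%, 40% or 60% of uninfected patients in both arms are scored as septic, measured rates are 32% vs 26%, 49% vs 44.5%, and 66% vs 63%. Detecting the same true effect on the measured endpoint then takes 897, 1929 or 3993 per arm.

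**4. Apparent benefit without fewer infections.** Let true sepsis stay at 10% in both arms while melatonin lowers *s* from 0.60 to 0.40. Measured sepsis is 0.10 + 0.90 × 0.60 = 64% against 0.10 + 0.90 × 0.40 = 46%. The 18-point difference is produced entirely by the definition.

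**The case against.** The strongest reply is about weight. Sepsis is one of five infectious items within a secondary endpoint of a 40-patient pilot whose primary aim is safety and tolerance. The other four (pneumonia, peritonitis, wound and urinary tract infection) are recorded separately and do not depend on the sepsis rule. A planner could size the next trial on those, or cross-tabulate sepsis with a recorded infection. The rates will be imprecise in any case: 2 events among 20 patients has an exact 95% interval of roughly 1% to 32%. All of this stands and limits the damage to the sepsis component and anything built on it. Recovery is incomplete, however, for an infection outside the four named categories.

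A second reply is that, under randomisation and blinding, misclassification should be similar in both arms. That holds for the response to surgery alone. It does not hold if the drug changes the signs themselves, which is what the Trial rationale proposes; blinding gives no protection there, because the definition creates the difference.

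Three stronger readings are tempting and not supported.
- A reader might take the Background to say that the response arises without infection. It does not. It also describes leakage of gut microflora and nearly certain transient endotoxinemia. That patients can meet two signs without infection is an inference, though a reasonable one.
- A reader might conclude that the sepsis rate will mostly measure surgical stress. No rate of meeting two signs is given, so this is true only at the higher assumed values of *s*.
- A reader might conclude that the infectious-complication rate as a whole is spoiled. The article lists components and defines no composite.

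**Conclusion.** The point holds: the sepsis rule needs no infection, yet its events are classed as infectious. Patients without infection can be scored as septic, in a number that the document does not give. The sepsis rate, and any combined rate that includes it, would be a misleading input to the planned power calculation. A lower rate under melatonin could not be read as fewer infections.

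The size depends on assumed rates. With *s* between 0.30 and 0.90, a true risk ratio of 0.50 is measured as 0.91 to 0.99. At *s* = 0.60, a planner who halves the observed rate arrives at 38 per arm where the true rate calls for 435.

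This should be fixed. It does not affect the primary safety aim, the four separately recorded infections or the validity of the randomised comparison as such.

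**What to change.** For the endpoint only, count sepsis when at least two of the four listed criteria are met and infection is documented or clinically suspected. State how suspicion is recorded, and that preventive antibiotics do not count as evidence of it; the Background mentions their use before or during surgery. Report the present rule separately as systemic inflammatory response, outside the infectious complications. This changes how events are counted, not how patients are treated.

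The cost is one sentence in the protocol, one eCRF field and a lower recorded sepsis rate. There is also retrospective work. Enrolment began in June 2007 at up to 5 patients per month, so by publication in January 2008, about 7 months later, up to about 7 × 5 = 35 patients may already have been enrolled. They would have to be reclassified from their records, and this should be done before unblinding.

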**Clinical outcome**			
Bilioma, pleural effusion, pneumonia, wound infection, peritonitis, UTI, sepsis			X
**Safety and Tolerance**			
Adverse events (AE)		X	X
*Liver*			
Integrity: AST, AP, GGT, ALT, LDH, GSH	X	X	X
Synthesis: CE, Chol, TP, PT, PTT albumin, CRP	X	X	X
Elimination: Bilirubin	X	X	X
*Kidney*			
Crea (blood), Na, K, Ca, Cl	X	X	X
Urea-N.	X	X	X
Crea (urine) for Crea-Clearance		X	X
*Substrates, metabolites, cytokines*			
Glucose, TG, lactate, IL-6, melatonin^2^	X	X	X
*Hematology*			
Hb, Hc, Thr, Leuko, Ery	X	X	X

^1 ^sampling at the same time each day, e.g. 8:00, ^2 ^sampling before, 2 h and 4 h after melatonin application

Pre-OP, pre-operative period; OP, operation/day of operation; Post-OP, post-operative period; OPS, "Operations- und Prozedurenschlüssel" [codes for operations and procedures]; UTI, urinary tract infection; AST, aspartate amino-transferase; AP, alkaline phosphatase; GGT, γ-glutamyl transferase; ALT, alanine aminotransferase; LDH, lactate dehydrogenase; GSH, glutathione; CE, choline esterase; Chol, Cholesterol, TP, total protein; PT, prothrombin time; PTT, partial thromboplastin time, CRP, c-reactive protein, Crea, creatinine; Na, natrium; K, kalium; Ca, calcium; Cl, chloride; Urea-N, urea-nitrogen; TG, triglyceride; IL, interlukin; Hb, hemoglobin, Hc, hematocrit, Thr, thrombocyte, Leuko, leukocyte; Ery, erythrocyte.

### Objectives and endpoints

The primary aim of this pilot study is to evaluate safety and tolerance of preoperative application of melatonin in patients undergoing operative procedures for partial liver resection. In addition, clinical parameters reflecting pathophysiological functions of the liver will be determined.

Data on clinical outcome (infectious and non-infectious complications) are collected as secondary endpoints to allow a power calculation for a randomized clinical trial aiming at clinical efficacy (Table 2).

### Randomization and blinding

Randomization (1:1) will be performed by the algorithm programmed in specific computer software and a randomization list will be prepared. Briefly, "blocked randomisation" will be performed using blocks of four that will include equal packages of test product and control product with the order of treatments within a block being randomly permuted, thus ensuring treatment group numbers are evenly balanced at the end of each block. The random number sequence is chosen to start from 1001 and sets an ascending allocation order for the first four subjects. Similarly, treatment type is allocated to the next four patients in the order specified by the next randomly selected permutation. The process is then repeated. The randomization list will be prepared by the institution that is responsible for the packaging of the study products (test product, placebo), i.e. the Pharmacy of the University clinic of Heidelberg, and kept in safe and confidential custody at this institution.

Patients satisfying the enrolment criteria will receive an ascending serial number in the order of their enrolment. Patient numbers for patients who replace drop-outs will be assigned similarly.

Both study products, test (melatonin) and placebo product (microcrystalline cellulose), will be of same form and appearance (white powder in sachets) including the packaging material.

In addition to the trial medication, the clinical trial director (PS) will receive a set of sealed envelopes, one for each randomization number. An identical set of sealed envelopes will be held at the Pharmacy of the University clinic of Heidelberg. These envelopes contain information on the subject's trial medication and are to be opened only under circumstances in which it is medically imperative to know what the subject is receiving.

### Adverse events

An adverse event (AE) is defined as any untoward medical occurrence in a subject administered a pharmaceutical product whether or not related to the investigational product including: new symptoms/medical conditions, new diagnosis, changes of laboratory parameters, intercurrent diseases and accidents, recurrence or worsening of pre-existing co-morbidities, increase of frequency or intensity of episodic diseases. A serious adverse event (SAE) is a life-threatening event resulting in death or significant persistent disability requiring subject hospitalization or prolongation of existing hospitalization. All AEs that occur after the subject has signed the informed consent document to participate in this evaluation of safety and tolerance of preoperative melatonin will be documented on the appropriate pages provided in the electronic Case Report Forms (eCRF). AEs must also be documented in the subject's medical records and must be monitored to determine outcome. The clinical course of the AE will be followed up until its resolution or normalization of changed laboratory parameters or until it has changed to a stable condition. SAEs must be reported using the "Serious Adverse Event" form provided in the eCRF. The initial report must be as complete as possible including details of the event and an assessment of the causal relationship between the event and the trial medication. The clinical trial director must also inform site monitor and data management in all cases.

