### Quality assurance

The procedures set out in this trial protocol, pertaining to the conduct, evaluation, and documentation of this trial, are designed to ensure that all persons involved in the trial abide by Good Clinical Practice [32] and the ethical principles described in the current revision of the Declaration of Helsinki [33]. The trial will be carried out in keeping with local legal and regulatory requirements.

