### Statistics and data management

All analyses will be carried out on an "intent-to-treat" basis. However, attempts will be made to analyze "per protocol" and "intent-to-treat" populations separately, when statistically appropriate. For the purpose of "per protocol" analysis, two groups of 20 eligible patients completing the protocol will be considered. Drop-out patients are not to be replaced.

The target variables of this trial include laboratory values, outcome parameters and adverse events. The target variables are measured from study day -1 to study day 7. The differences of the laboratory values between study day -1 and 7 are tested with the paired t-test or, in case of uneven distribution, the Wilcoxon-test (2-sided) for within group comparison. The Mann-Whitney U test will be used to detect differences between treatment groups. The following statistical values will be calculated when appropriate: mean, standard deviation, 95%-confidence interval of the mean, minimum, lower quartile, median, upper quartile, maximum, valid number, frequency count, and percentage. The laboratory values will be counted according to their normal ranges (below normal, normal, and above normal). SAS software (Version 8.2) will be used for analysis.

All patient data (clinical and resource use) generated during the study will be recorded on the eCRFs provided by HealthEcon AG, Basel, Switzerland. These forms are specifically designed in Microsoft Office Access (Version: 1.01) to meet the data recording requirements of the clinical study protocol. Corrections of wrong entries will be recorded automatically. In addition, for any correction of data concerning "Adverse Events" or the primary target variable the reason for the correction must be entered. All data will be entered into a central database as recorded.

All data management activities will be done according to the current Standard Operating Procedures (SOPs) of HealthEcon AG.

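### The SAE definition reads as cumulative conditions, so an event meeting only one seriousness criterion would be misclassified as non-serious

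*Protocol article*

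**What the plan says.** Only the protocol article is at hand. Its Adverse events section gives one definition of seriousness: an SAE "is a life-threatening event resulting in death or significant persistent disability requiring subject hospitalization or prolongation of existing hospitalization". No other section restates or replaces it.

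The same section attaches duties to the class. SAEs go on a dedicated eCRF form, and the initial report must describe the event and assess its causal relationship to the trial medication.

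The surrounding text matters for judging the consequences:

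- Objectives and endpoints: "The primary aim of this pilot study is to evaluate safety and tolerance".
- Adverse events: documentation covers "All AEs that occur after the subject has signed the informed consent document". Events are also entered in the medical record and followed until they resolve or stabilise.
- Statistics and data management: "The target variables of this trial include laboratory values, outcome parameters and adverse events".
- Methods/Design: bleeding, bile fistula and pneumonia are among the clinical outcome parameters. Objectives and endpoints makes infectious and non-infectious complications secondary endpoints.
- Quality assurance: the procedures are meant to ensure that "all persons involved in the trial abide by Good Clinical Practice". No seriousness criteria are given there.

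**The concern.** Seriousness criteria do their work as a list in which any one is enough. Here they are run together. An event must be life-threatening, must result in death or lasting disability, and must require or prolong a hospital stay. The sentence also strains against itself, since a death does not require hospitalization.

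What is at stake is which events enter the SAE class. An investigator who follows the text has no stated duty to file the SAE form and causality report for a survived life-threatening event, or for a complication whose only serious feature is a longer stay. Colleagues who follow habit would file one. Classification would then vary between staff, and any table of SAEs would understate harm in a trial whose primary question is safety.

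**Working it through.** There is no figure in the article to reproduce, because the point concerns wording. The check treats the definition as a logical rule and asks which events satisfy it.

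**Inputs.** Five criteria, all taken from the sentence in Adverse events: life-threatening (L), death (D), significant persistent disability (S), hospitalization (H) and prolonged hospitalization (P). The number of non-empty combinations is 2^5 − 1 = 31.

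**Readings compared.**

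| Reading | Rule | Combinations that qualify | Single-criterion events that qualify |
|---|---|---|---|
| Literal chain | L and (D or S) and (H or P) | 1 × 3 × 3 = 9 of 31 | none |
| Hospital clause attached to disability only | L and (D, or S with (H or P)) | 8 + 3 = 11 of 31 | none |
| Prolongation detached as its own criterion (strained) | (L and (D or S) and H) or P | 16 + 3 = 19 of 31 | prolongation only |
| Alternatives | L or D or S or H or P | 31 of 31 | all five |

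In the second row, 8 is the number of combinations with L and D present and the other three free (2^3), and 3 is L and S without D, with H, P or both. In the third row, 16 is every combination with P (2^4), and 3 is L and H without P, with D, S or both.

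These are unweighted combinations, not event frequencies, and some are formal only. Death without threat to life, for example, accounts for 2^3 = 8 of the 31. Removing those leaves 23, and the literal chain still admits 9 and the second reading 11, because both require L.

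**Examples from the trial's own complication list.**

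- Bleeding that threatens life, with full recovery: L is met, D and S are not. It fails the first two readings whatever happens to the length of stay.
- Pneumonia that lengthens the stay without threatening life: only P is met. It fails the first two readings and passes only the strained one.
- A death in a patient already in hospital whose stay is not prolonged: L and D are met, H and P are not. It fails the literal chain and passes the second reading, so even this case depends on how the sentence is parsed.

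**Illustration of size (assumed, not in the article).** Take 20 patients per arm (40 in total, 1:1), a true per-patient SAE risk p, and a fraction f of those patients captured by the wording. The expected count is 20pf, and P(at least one) = 1 − (1 − pf)^20.

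| p | f = 1 | f = 0.5 | f = 0.25 | f = 0.1 |
|---|---|---|---|---|
| 0.1 | 2.0; 0.88 | 1.0; 0.64 | 0.5; 0.40 | 0.2; 0.18 |
| 0.2 | 4.0; 0.99 | 2.0; 0.88 | 1.0; 0.64 | 0.4; 0.33 |
| 0.4 | 8.0; 1.00 | 4.0; 0.99 | 2.0; 0.88 | 0.8; 0.56 |

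Each cell gives the expected number of patients with an SAE per arm, then P(at least one). The article supports no particular row or column. The table shows only how the SAE count would respond.

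**The case against.** The strongest reply is that little depends on the SAE label. The article makes no SAE count an endpoint, a comparison or a stopping trigger. The safety block of Table 2 consists of all adverse events plus liver, kidney, metabolic and haematology values, and the wording filters none of these. Every adverse event is documented and followed up, and bleeding, bile fistula and pneumonia are collected separately as outcomes. All of this stands. A reader might infer that the trial would report a falsely clean safety record, or that a real difference between arms in such complications would be invisible. The documents do not support that: the difference would be missing from SAE counts but present in the adverse event and complication data.

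A second reply is that the sentence looks like a list that lost its separators in condensation, and that the full protocol or the SAE form may have it right. That is possible and cannot be checked here. It does not remove the point, because the defect is a rule stated wrongly in the current text, not a detail left out, and the article offers nothing to correct it.

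A third reply is that the Good Clinical Practice commitment governs. It is general, sits beside an explicit definition and does not override it. Equally, a reader might infer that the sentence contradicts that standard. The standard's content is not reproduced in the article, so this point does not rest on it.

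**Conclusion.** The point holds as a defect of definition. On either ordinary reading, no event that meets only one of the named criteria is serious. Even the most generous reading admits just one of the five. The result is misclassification, SAE forms and causality reports that the text does not call for, and an understated SAE tabulation if one is made. It is not loss of data, and the recorded events could be reclassified later. An initial SAE report that was not made at the time cannot be restored that way.

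The size cannot be stated. A reader might infer that most serious events would be missed, but the article gives no complication or SAE rates, and the count of combinations is not a frequency. Nor can late reporting be inferred, since the article sets no deadline for SAE reports.

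The conclusion assumes that staff apply the sentence as written and that the eCRF form does not already carry a different definition.

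**What to change.** Rewrite the definition with the criteria it already names as separate alternatives: an adverse event is serious if it results in death, or is life-threatening, or results in significant persistent disability, or requires hospitalization or prolongs an existing stay. Then check that the eCRF SAE form and any SAE tabulation use the same wording. Enrolment began in June 2007, so adverse events already recorded should be reclassified under the corrected definition and any missing SAE forms completed.

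The cost is one sentence, one form check and a pass through the existing adverse event records. More SAE forms will be filed and the reported SAE rate will be higher. Randomization, sample size, endpoints and analysis methods are unchanged.
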